4. To compare the psychometric properties (sensitivity, specificity, cutoff points) of paper-based ALPHA and EPDS *versus* the e-version administered to medically low- and high-risk pregnant women	Are the psychometric properties (for example, sensitivity, specificity, cutoff points) similar or better in the ALPHA and EPDS e-version compared to the paper-version when administered to pregnant women?	Psychometric properties: sensitivity, specificity of ALPHA and EPDS in paper-based and e-versions	ALPHA, EPDS, MINI	The psychometric properties of e-version of ALPHA and EPDS are similar or better compared to paper-based version
5. To compare the cost-effectiveness e-screening compared to paper-based screening	Is e-screening as a component of routine prenatal care cost effective when compared to paper-based screening?	Cost-effectiveness: actual costs	The expected incremental cost effectiveness of e-screening is cost effective at values of health considered acceptable in the Canadian healthcare system	E-screening will be cost effective

ALPHA: Antenatal Psychosocial Health Assessment; CAE: CASI Assessment Evaluation; DES: Disclosure Expectations Scale; EPDS: Edinburgh Postnatal Depression Scale; MINI: Mini International Neuropsychiatric Interview.

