#### *The control group*

Women in the control group will complete paper-based versions of the ALPHA and EPDS. Usual prenatal care at our clinic recruitment sites involves women self-completing the ALPHA on a single occasion during pregnancy, typically while they wait for their first or second prenatal visit. At the hospital recruitment site, usual care does not include formal screening, although women’s mental health status is monitored due to the high medical risk. Paper-based screening was chosen as the comparator because the primary objective of the study is to assess feasibility and acceptability of the electronic administration of a psychosocial assessment.

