### Secondary outcomes

The five secondary outcomes are (see measures in Table 1b):

(1) the proportion of pregnant women scoring 13 or more on the total EPDS, 4 or more on the anxiety subscale, and identified as some or high psychosocial risk on the ALPHA;

(2) the level of disclosure as assessed by mean scores on the Perceived Risk and Perceived Utility subscales of the Disclosure Expectations Scale (DES) [55]. The DES is an 8-item scale designed for evaluation of the perceived risk (items 1, 2, 4, and 5) and benefit (items 3, 6, 7, and 8) of disclosure. Convergent validity of the subscales has been demonstrated with other measures of self-disclosure, as well as psychological distress, and intention to seek mental healthcare [55];

(3) description of factors that significantly increase the odds of acceptability, feasibility, and disclosure related to each form of screening;

(4) psychometric properties (for example, Cronbach’s alpha, sensitivity, specificity, positive and negative predictive values) of the e-version of the EPDS and ALPHA. A scoring algorithm does not currently exist for the ALPHA (for example, the trained provider subjectively judges risk based on responses); however, an algorithm would promote standardization in clinical decision-making and efficiency since a score could be calculated as part of e-screening. We plan further tool development comprising derivation of a quantitative scoring method for classifying women into psychosocial risk categories; and

(5) cost-effectiveness of detecting clinical depression and anxiety in e-screening *versus* usual screening (that is, equipment and human resource costs of e-screening *versus* paper-based - see Secondary outcomes).

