**Psychometric properties** Psychometric properties of internal consistency (Cronbach’s alpha; item-total correlation) will be calculated for the EPDS by modality. Predictive validity measures of sensitivity, specificity, positive predictive value, and negative predictive value will be calculated using clinical interview diagnosis as the reference. Comparisons of the psychometrics between the two modalities will be made by correlational analysis using Cohen’s guidelines [59]. In terms of further tool development of the ALPHA, we will develop an integer score-based prediction rule for the prevalence of anxiety and depression, according to MINI diagnosis. This method was previously used to develop a prenatal screening tool for postpartum distress by two members of the research team (SM, DK) [60]. We will develop a best fit multiple regression model predicting depression and/or anxiety as per clinical interview diagnosis, candidate variables for which will be drawn from the ALPHA. A regression coefficient-based scoring algorithm [60] will be applied to the final regression model in order to develop a single screening score. Receiver operating characteristic (ROC) analysis will then be used to determine an optimal cutoff for the screening score. Finally, we will perform a ROC analysis for each modality (e-version *versus* paper-based) and compare indices of sensitivity, specificity, positive and negative predictive values using Cohen’s guidelines [60]. All analyses will be conducted in the total sample, with subgroup analyses conducted by medical risk to determine whether the scoring is robust across risk subgroups.

##### 

**Cost-effectiveness** For the economic analysis, we will estimate the incremental costs-effectiveness (ICER) for the e-screening alternative compared to the paper-based alternative. The e-screening costs include investment costs to technology (programs, tablets, data storage) and the operating costs at the clinic that may differ somewhat from the conventional group administrative and analytical cost. Cost-effectiveness is determined by incremental cost to identify a woman with increased risk of prenatal and postpartum depression and anxiety. Because we are not going to follow up the screened women, the costs and outcomes after the screening are not included in this initial economic analysis.

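### Cost-effectiveness is to be judged against accepted values of health, but the ICER is a cost per woman identified and nothing after screening is measured, so the stated criterion cannot be applied

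*Protocol article*

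**What the plan says.** In Table 1b, the row for objective 5 gives the outcome as "Cost-effectiveness: actual costs", with no unit of effect. Its measure column reads "The expected incremental cost effectiveness of e-screening is cost effective at values of health considered acceptable in the Canadian healthcare system", and its hypothesis is "E-screening will be cost effective".

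The Cost-effectiveness paragraph of the Analysis section defines the result differently: "Cost-effectiveness is determined by incremental cost to identify a woman with increased risk of prenatal and postpartum depression and anxiety". It then limits the scope: "Because we are not going to follow up the screened women, the costs and outcomes after the screening are not included" in what it calls an initial analysis. That paragraph takes the paper-based alternative as comparator.

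Item 5 under Secondary outcomes states the effect as detection of clinical depression and anxiety. It names the comparator as "usual screening (that is, equipment and human resource costs of e-screening" set against paper.

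The control group section says that the paper arm completes both the ALPHA and the EPDS. It describes usual care at the clinics as self-completion of the ALPHA, once in pregnancy. Of the antenatal unit it says: "At the hospital recruitment site, usual care does not include formal screening".

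Under Data collection procedures, economic data come from program accounts (technology and software) and from staff interviews on clinic operating costs for the two alternatives. Women complete the assessment once, and no quality-of-life or utility instrument is listed.

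**The concern.** A value of health is a price per unit of health gained. The planned ICER is a price per woman identified. If the two are in different units and the trial gathers nothing that links them, the criterion in Table 1b cannot confirm or refute the hypothesis beside it.

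The practical risk lies in reporting. A modest cost per woman identified could be presented as good value for the Canadian system, although neither the benefit nor the cost of acting on a positive screen has been counted. The loose comparator label adds a second risk: a tablet-versus-paper result could be read as a comparison with current practice.

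**Working it through.** The protocol states no ICER, threshold or economic sample size, so there is no economic figure to reproduce. The check is one of units and definitions.

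**1. What the analysis will produce.** Let ΔC be the difference in cost and ΔD the difference in women identified, tablet minus paper. The planned result is

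ICER = ΔC / ΔD, in dollars per additional woman identified.

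**2. What the criterion needs.** A value of health λ is in dollars per unit of health. To apply it to this ICER one needs g, the mean health gain per woman identified, and c, the mean cost per woman identified after screening. The highest acceptable ICER is then

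λ × g − c.

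Neither g nor c is in the protocol. Both belong to the period after screening, which the Analysis section excludes.

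**3. How much turns on the missing link.** All values here are assumptions for illustration. Take λ from 20,000 to 100,000 and g from 0.005 to 0.1 units of health, with c set to 0.

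| λ | g = 0 | g = 0.005 | g = 0.01 | g = 0.05 | g = 0.1 |
|---|---|---|---|---|---|
| 20,000 | 0 | 100 | 200 | 1,000 | 2,000 |
| 50,000 | 0 | 250 | 500 | 2,500 | 5,000 |
| 100,000 | 0 | 500 | 1,000 | 5,000 | 10,000 |

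For non-zero g the acceptable cost per woman identified runs from 20,000 × 0.005 = 100 to 100,000 × 0.1 = 10,000, a 100-fold range. At fixed λ, g alone moves it 20-fold (0.1 / 0.005). Any positive c lowers every entry.

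**4. When no threshold is needed.**
- ΔC < 0 and ΔD > 0: the tablet dominates on cost and women identified.
- ΔC > 0 and ΔD < 0: paper dominates.
- ΔC and ΔD of the same sign: a threshold per woman identified is needed, and a value of health does not supply one.

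Even in the first case the conclusion is about cost and identification. It does not reach value in health terms, because the extra women identified bring later costs and benefits that are not counted.

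**5. Two effect definitions.** Secondary outcomes, item 5, counts clinical depression and anxiety. The Analysis section counts women at increased risk. These are different denominators: a woman can be flagged as at risk without having a diagnosis. The tablet could therefore raise the number flagged without raising the number of diagnosed cases detected.

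**6. The comparator label.**

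| Setting | Usual care as described | Paper arm |
|---|---|---|
| Maternity clinics | ALPHA (EPDS not named) | ALPHA + EPDS |
| Antenatal unit | No formal screening | ALPHA + EPDS |

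For the unit the mismatch is stated outright. For the clinics it is inferred from the EPDS not being named.

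**The case against.** The strongest reply is that this is the last of five secondary objectives, that the Analysis section calls the work initial and openly declares what it excludes, and that a journal article may leave a numerical threshold to a fuller plan. The last part stands: the absence of a threshold is not counted here. But a threshold would not cure the problem, because the stated analysis has no means of converting its unit into health. The exclusion is disclosed in one place while the criterion in Table 1b was not narrowed to match.

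The comparator was also chosen deliberately. Table 1b, the control group section and the Analysis section all name paper, and item 5 explains its one use of the usual-screening label as paper in the same sentence. This stands. Paper is the right comparator for a question about mode of delivery, and the label is a slip of wording.

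Four stronger readings are tempting and not supported:
- *That no economic comparison is possible.* Tablet versus paper can be estimated as cost per woman identified.
- *That every ICER fits either conclusion.* This fails under dominance.
- *That the label is wrong for the whole sample, or for a known share of it.* The clinic part is an inference. Hospital intake is 45 of 95 new patients a month, but the protocol gives no recruitment split between the settings, so no share follows.
- *That the trial should compare the tablet with each site's actual usual care.* That is a different question. Costs are gathered for the two alternatives only, and no unscreened women are observed.

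**Conclusion.** The point holds for the criterion and the hypothesis as written. A cost per woman identified, with later costs and outcomes excluded and no utility measure collected, cannot be judged against values of health. Only dominance on cost and women identified could be shown without a further threshold, and that would still not be a finding about value in health terms.

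Two smaller inconsistencies belong with it: the effect is defined in two ways, and the usual-screening label contradicts the stated hospital practice and appears to differ from clinic practice.

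The size is that of one secondary objective. Recruitment, randomisation and the other outcomes are untouched, but the trial's permissible economic conclusion is narrower than Table 1b promises. The contradiction rests on the protocol's own text. The 100-fold range rests on assumed inputs and serves only to show that the missing link cannot be ignored. It should be corrected before the economic results are written up.

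**What to change.** - **Table 1b, objective 5.** Restate the objective, outcome and hypothesis as incremental cost per additional woman identified, tablet versus paper-based ALPHA plus EPDS. Delete the values-of-health criterion and the unqualified claim of cost-effectiveness.
- **Secondary outcomes item 5 and the Analysis section.** Use one definition of effect in both: either women flagged as at increased risk, or women flagged and confirmed at the diagnostic interview. Planned data can support either, since all women are to have the MINI.
- **Secondary outcomes item 5.** Replace the usual-screening label with paper-based ALPHA plus EPDS.
- **Reporting.** Give the two components before any ratio: the cost difference with a sensitivity range, and the difference in women identified with a 95% CI. A range suits the costs because they come from accounts and staff interviews, with no patient-level costs described that would support a sampling interval.
- **Do not add** rows for each site's usual care, since the trial collects no data for them.

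The cost is a few lines of wording, with no new data collection. The downside is that the trial gives up a headline claim of value for money; that would need health outcomes and costs after screening, which this analysis does not cover.

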## Methods/Design

### Study design

The study is a parallel-group, randomized, controlled superiority trial (RCT) with a qualitative descriptive component (Figure 1). This design is well-suited for answering questions of effectiveness, acceptability, and feasibility [47]. In this trial, physicians and all research assistants conducting diagnostic interviews are blinded. We adhered to CONSORT guidelines in the design of the trial [45,46] and the SPIRIT guidelines [48,49] in reporting its details in this protocol. Approval for this study was granted by the Human Research Ethics Board at the University of Alberta.

**Figure 1 F1:**
[figure not shown]
**CONSORT trial flow diagram.** *ALPHA: Antenatal Psychosocial Health Assessment; EPDS: Edinburgh Postnatal Depression Scale; MINI: Mini International Neuropsychiatric Interview.

### Randomized controlled trial

#### *Eligibility criteria*

Pregnant women are eligible for this study if they: (1) receive care at one of the recruitment sites; (2) are able to speak/read English; (3) are willing to be randomized to e-screening; and (4) are willing to participate in a follow-up diagnostic interview within 1 week of recruitment.

#### *Setting*

Recruitment of pregnant women will take place at maternity clinics in a large, urban Canadian city and an inpatient, high-risk antenatal unit in a tertiary care hospital. Medically high-risk pregnant women have significantly higher rates of depression and anxiety than low risk women [45,46]. Thus, recruiting women with low and high medical risk will enable us to evaluate the effectiveness of e-screening to accurately detect symptoms of depression, anxiety, and psychosocial risk across the spectrum of low to high symptom prevalence and severity. All sites serve a sociodemographically diverse population. At the maternity clinics, family physicians specializing in obstetrics provide full obstetrical care (for example, all prenatal, delivery, and postpartum care) and shared care (for example, they provide prenatal care up to 28 weeks and then care is transferred to an obstetrician). The high-risk antenatal unit is a 24-bed inpatient unit in a large, tertiary care hospital with over 5,900 births per year. It is the only inpatient acute hospital in the community and surrounding region for women with high-risk pregnancies, and women receive care primarily from obstetricians. The majority of family physicians, obstetricians, and nurses at the recruitment sites do not have specialized training in mental healthcare.

#### *Recruitment procedures, consent, randomization, and allocation procedures*

Recruitment procedures are similar across sites. Trained staff at the recruitment sites will use a standardized script to determine each eligible (see Eligibility criteria) woman’s interest in study participation. Women will be referred to an onsite research assistant who will provide the tablet. Women will complete the consent electronically on the tablet and receive the automatically generated copy via email. The research assistant will be available to answer questions about study participation and tablet logistics. A simple, computer-generated randomization process designed by the Women’s and Children’s Health Research Institute (WCHRI) at the University of Alberta allocates women (1:1 ratio) automatically to the control or intervention group, and they will receive a ‘pop-up’ message informing them that they will complete questions about emotional health on paper (control group) or tablet (intervention group). Computerized randomization preserves allocation concealment and reduces the possibility of selection bias since the research assistant is kept unaware of the group assignments until after the participants are allocated to groups.

#### *The intervention*

The intervention is psychosocial assessment via electronic administration. Women assigned to the intervention group will complete the psychosocial assessment comprising the ALPHA and the EPDS electronically using a computer tablet. Rather than the traditional, sole use of symptom-based mental health screening tools, the combined use of a psychosocial risk assessment instrument (for example, ALPHA) that detects current and future risk for mental health problems and a symptom screening tool (for example, EPDS) that detects current symptomatology has been recommended as the most effective, comprehensive approach to psychosocial assessment [3].

The ALPHA was selected for use as a psychosocial risk assessment tool because its paper-based version is currently used in our clinic recruitment sites. In addition, the ALPHA is a Canadian-developed tool that has been tested in the Canadian context in primary care [13,30] and has been gaining popularity for antenatal psychosocial assessment in these settings. It was designed to identify psychosocial risk factors in pregnant women that may increase their risk for adverse psychosocial outcomes (for example, stressful life events, lack of support), including postpartum depression [50,51]. It has undergone extensive face and content validity by experts including obstetricians, family physicians, and midwives [30], and identifies significantly more cases of psychosocial risk than non-standardized assessment [51]. The majority of providers indicated that the tool could readily be implemented in routine prenatal care and pregnant women found it acceptable [33]. The self-report version used in this study is easily completed in 5 to 10 minutes. It asks women questions on the topics of family life, stressors, feelings about the pregnancy, substance use, abuse, and family of origin. Women respond with yes/no or 6-point Likert-scale options. Based on a review of responses in each category, trained providers subjectively judge whether women are at low, some, or high psychosocial risk. No cutoff points or scoring algorithm have been developed and thus sensitivity and specificity data are not available. Risk categories are then used to create a care plan.

The 10-item EPDS was selected for evaluation because it is one of the most widely used screening instruments for postpartum, and less commonly, prenatal depression. The EPDS was designed as a brief tool to screen for postpartum depression symptoms within the previous 7 days [52]. A score of 13 or greater (range, 0 to 30) is a well-established cutoff for clinically significant depression symptoms consistent with meeting criteria for a major depressive episode [52]. Original psychometric testing resulted in sensitivity of 85%, specificity of 77%, the positive predictive value of 83%, split-half reliability of 0.8, and a Cronbach’s alpha of 0.87 [52]. The 3-item anxiety subscale of the EPDS is a reliable and valid tool for probable anxiety using a cutoff of 4 or more with a Cronbach’s alpha of 0.74, sensitivity of 66.7%, and specificity of 73.2% [35,53].

#### *The control group*

Women in the control group will complete paper-based versions of the ALPHA and EPDS. Usual prenatal care at our clinic recruitment sites involves women self-completing the ALPHA on a single occasion during pregnancy, typically while they wait for their first or second prenatal visit. At the hospital recruitment site, usual care does not include formal screening, although women’s mental health status is monitored due to the high medical risk. Paper-based screening was chosen as the comparator because the primary objective of the study is to assess feasibility and acceptability of the electronic administration of a psychosocial assessment.

#### *Procedures*

##### 

**Maternity clinics** At the maternity clinic recruitment sites, each eligible woman will complete the ALPHA and EPDS while they wait for their prenatal appointment - either via computer tablet or paper. After randomization to the control group, a message appears on the tablet, directing women to complete the ALPHA and EPDS on paper. An automatic ‘skip’ procedure ensures that the electronic versions of the ALPHA and EPDS are bypassed for women in the control group. Following completion of the paper-based psychosocial assessment, women will proceed to complete the baseline questionnaire on the tablet. Women in the intervention group will be directed to answer questions about emotional health (ALPHA and EPDS) and the baseline questionnaire on the tablet. All questions require responses, and thus women cannot proceed past questions with missing answers until completed. In keeping with the current clinic processes of including the assessment in the medical record, the electronic copy will be printed following completion. As is usual care in the maternity clinics, a Registered Nurse will review the assessment, judge whether women are at low, some, or high risk, discuss women’s psychosocial assessment responses with them, and provide follow-up referrals for those with some or high psychosocial risk with a mental health nurse affiliated with the clinic.

##### 

**Hospital-based antenatal unit** In the antenatal unit, the research assistant will meet with women who have agreed to a follow-up contact by the research team. The research assistant will provide the tablet, a copy of the paper-based questionnaire, and an opaque envelope. The research assistant will be available to answer questions related to study participation, but then will leave the room to allow the woman to proceed to the computer randomization, and complete the assessment and baseline questionnaire independently. Thus, the research assistant will have no knowledge of the woman’s group assignment. Following randomization to the intervention group, women will be directed by a computer message to complete the ALPHA and EPDS on the tablet as well as the baseline questionnaire. Women assigned to the control group will be directed by a computer message to complete the ALPHA and EPDS on paper and then return to the tablet for completion of the baseline questionnaire. An automatic ‘skip’ procedure ensures that the electronic versions of the ALPHA and EPDS are bypassed for women in the control group.

In both cases, prior to the final submission of the baseline questionnaire, intervention and control group women will be prompted to place the paper-version questionnaire in the opaque envelope and seal it.

In the antenatal unit setting, procedures to maintain blinding of the research assistant are required because he/she will be both recruiting women and conducting the follow-up diagnostic interview. Blinding of the research assistant is maintained by: (1) distributing an opaque envelope and a paper-based version of the ALPHA and EPDS to all participants prior to randomization; (2) using a computer-based randomization process that reveals the assignment to the woman, but not the research assistant; (3) instructing all women to return the paper-based assessments to the envelope prior to giving the tablet and envelope back to the research assistant (an electronic message on the tablet prompts women to return the paper-based assessment to the envelope); and (4) training the research assistant to return all envelopes (unopened) to the research coordinator.

Two processes have been designed to ensure that the correct versions of the ALPHA and EPDS are completed (for example, paper *versus* electronic) and to avert the possibility that participants might self-select a preferred version: (1) the electronic versions of the ALPHA and EPDS are not available to women in the control group through a programmed ‘skip’ procedure; and (2) the research coordinator will conduct a manual check on a subset of 30 control group participants at three different times in the course of the study to ensure that paper-based versions of the ALPHA and EPDS are completed.

If women are identified as meeting criteria for a mood or anxiety disorder on the MINI International Neuropsychiatric Interview (see Confirmation of diagnosis) or if they score 13 or more on the EPDS the research assistant will create a referral for the woman (with her permission) to the hospital-based reproductive mental health support program and she will be followed up by a mental health therapist.

